### ***Process/health system outcomes***

In this project, we will access administrative healthcare data for participant ED visits. ED data will be reviewed for participants who consent/assent to medical record review. We will measure the following outcomes:

- Number of children/youth per month discharged ASQ at triage (low-risk screening outcome) to urgent care follow-up clinic
- Number of children/youth per month who receive psychiatry consultation in the ED after HEADS-ED assessment
- Number of children/youth per month discharged to urgent care clinic after HEADS-ED assessment
- Number of children/youth per month discharged with another recommendation after HEADS-ED assessment, and documentation of the recommendation
- Number of ED visits per month for child/youth mental healthcare that concluded in admission to each children's hospital or transfers to admit at another institution
- Length of ED stay (the interval between time of ED arrival and time of ED departure, either admission or discharge; in minutes) for visits per month to each children's hospital
- Proportion of discharged children/youth who received urgent care clinic follow-up within 48 hours
- Number of child/youth receiving follow-up mental healthcare within 7 days of the ED visit (to be reported by parents/caregivers at 1-month follow-up)
- Number of child/youth receiving follow-up mental healthcare that relates to their index ED visit, within 7 days and 1 month of the index visit
- Appropriate care in the appropriate setting. Research assistants will audit all ED/clinic records monthly at each site and document whether assessments children/youth received are congruent with discharge recommendations
- Type of follow-up care accessed. Parents/caregivers will report types of follow-up care within a month after an ED visit or urgent clinic follow-up appointment

### ***Cost outcomes (Economics Sub-Project)***

This sub-project will involve a focused, conservative approach to costing by only examining child and youth mental healthcare use, not examining all service use. Investigators from the Institute of Health Economics will prepare a separate protocol for this sub-project.

### ***Balancing measures (Economics Sub-Project)***

Investigators from the Institute of Health Economics will document the number of ED revisits for mental and substance use disorders, suicide attempts (ED visits for self-harm), and completed suicides within 1 month of the index ED visit. ED revisits and suicide attempts will be determined using data provided from Alberta Health. The results will be shared with the PACMAN team to identify any unintended consequences of our care bundle.

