### 2.1 Improvements to triage in the ED

In the bundle, triage nurses will use the Ask Suicide-Screening Questions. The ASQ tool is validated for pediatric ED patients and is used in many EDs across the US based on its ability to accurately screen for suicide risk among children and youth seeking care. Because healthcare providers differ in how they ask questions, and patient responses are influenced by how questions are posed, a standard approach to risk screening using a robust tool (i.e., the ASQ) identifies patients at risk more accurately. For triage nurses who feel ill-equipped about assess a child/youth's risk, the ASQ is an important tool. In hospitals that use the ASQ, staff report being very comfortable asking the questions. The tool requires minimal training. The goal of the screening is to identify children and youth who require further ED-based assessment to determine the actual level of risk.

The ASQ consists of four yes/no questions, takes 20 seconds to administer, and is available in 13 languages. A child/youth who answers, "Yes" to any question or refuses to answer one, is considered to be 'high risk'. Such children/youth have a threefold high risk for suicide. Children who reply "No" to all questions are considered to be 'low-risk'.

**At Alberta Children's Hospital**, children and youth who screen low-risk on the ASQ will be given a **booked appointment within 24-48 hours at an urgent care clinic** (a partnered mental healthcare clinic located nearby that permits real-time scheduling by ED staff). This approach will ensure families can discuss their needs and concerns—this currently does not occur for low-risk concerns. Families will meet with a nurse or social worker to review the details of their appointment (e.g., date, time, location, and name of clinic staff), and will leave the ED within 30 minutes of arrival.

**At Stollery Children's Hospital**, children and youth who screen low-risk on the ASQ will be able to go to the co-located mental health clinic (located in the hospital) during the clinic's hours. During off-hours, these children and youth will be given a **booked appointment within 24-48 hours at an urgent care clinic** (a partnered mental healthcare clinic located nearby that permits real-time scheduling by ED staff).

ACUTE MENTAL HEALTH BUNDLE **EMERGENCY DEPARTMENT**

[figure not shown]

Figure 1. Care bundle implementation

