## 2.2 Improvements to ED care

In the acute mental healthcare bundle, children and youth who screen high-risk on the ASQ **will not undergo medical clearance**. They will directly see a mental healthcare provider (e.g., psychiatric nurse, social worker) for a focused mental health assessment using the HEADS-ED tool.

The HEADS-ED mnemonic (Home, Education, Activities/Peers, Drug/Alcohol, Suicidality, Emotions and Behaviour, Discharge Reasons) is recommended for ED-based assessments. It improves communication, expedites decision-making, and guides the use of healthcare resources. Using the tool requires minimal training, and on average, should focus the mental health assessment so that it takes ~20 minutes to complete.

The HEADS-ED tool generates a total score and *action level* for the child/youth's concerns by summing the scores in each area in the mnemonic: 0 (*no/minimal functional impairment and no need for action*), 1 (*moderate functional impairment and needs action but not immediate*), or 2 (*severe functional impairment/needs immediate action*).

A total sum score <8 or 'suicidality' score of 0 or 1 will result in a 24-48 hour follow-up appointment in an urgent care clinic. ED physicians will provide medical evaluation if a concern emerges during the assessment or at the request of the family. This approach to assessment is expected to expedite mental health assessment, reduce ED physician costs, shorten ED length of stay, and provide families with follow-up after the ED visit.

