### 3.5 Bundle exclusion criteria

Children and youth not eligible to receive the care bundle will receive acute care following institutional policies. Approximately 20% of all mental health visits (based on site-specific data and the literature) will be by children/youth in an ineligible category:

- a) Brought to the ED by police or peace officers – they bypass triage, go straight to a room, are often restrained, are being held involuntarily, and require urgent physician assessment
- b) Held under Form 10
- c) Features of schizophrenia, schizotypal and delusional disorders (psychosis)
- d) Behavioural syndromes associated with physiologic disturbances (e.g., eating disorders)
- e) Significant intentional self-harm (e.g., laceration, ingestion, hanging)
- f) Previous participation in the study

Patients who do not meet the inclusion criteria and/or who are excluded based on at least 1 exclusion criterion will undergo traditional local care approaches that include physician assessment following triage in keeping with current standards of ED care. In addition, at any point in time, should the patient/family/healthcare team desire deviation from the acute mental healthcare bundle, the family can be switched into the traditional ED care track and based on acuity/urgency, an ED physician will provide a medical evaluation.

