### ***Administrative***

Daily medical record review by research assistants will include collecting data on the number of bundle-eligible children/youth, number of children/youth with urgent clinic appointment booked based on ASQ screen at ED triage, and HEADS-ED assessment outcomes. Administrative databases will be accessed to collect: length of ED stay, time of admission to ED, time of discharge from ED, the Canadian Triage and Acuity Scale (CTAS) and the number of children/youth who received urgent care clinic appointment within 48 hours. Also, data will be collected for any ED visits within 30 days of the participants' index ED visit including the re-presentation visit triage date and time, the chief complaint, admission status, CTAS score, and discharge diagnosis. The Calgary team will access Edmonton's site participants' ConnectCare for the data collection within 30 days of the index ED and also the CTAS score from the index ED visit.

The PI will provide the full name, age, and Alberta personal health number (PHN) of study participants enrolled in the pre-implementation bundle and post-bundle implementation periods with Alberta Health to enable linkage to administrative healthcare databases in the economics analysis project (e.g., NACRS, ACCS, DAD, Alberta Health, Coroners' Data).

To enable the analysis in the economics sub-project, the PI will provide investigators at the Institute of Health Economics with study participants':

1. Study screening ID (generated for study administrative purposes)
2. Date of enrolment (to confirm study phase)
3. Assigned cohort (pre-implementation or post-implementation; to confirm study phase)
4. Age and gender

5. Forward sortation data (participant disclosed 3 first digits of postal code) at time of enrolment

6. Well-being scores

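### The balancing measures contain no medical event although the bundle drops routine medical clearance; medical returns to an ED are recorded, but no outcome or analysis treats them as a harm

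*Protocol*

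**What the plan says.** Protocol 3.8 (Balancing measures) lists three event types within one month of the index visit: "the number of ED revisits for mental and substance use disorders, suicide attempts (ED visits for self-harm), and completed suicides". It states their purpose: "The results will be shared with the PACMAN team to identify any unintended consequences of our care bundle". No other section assigns measures to that purpose.

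Protocol 2.2 says that ASQ high-risk children "will not undergo medical clearance" and go directly to a mental healthcare provider. A physician route remains: "ED physicians will provide medical evaluation if a concern emerges during the assessment or at the request of the family". Protocol 3.5 adds that at any point "the family can be switched into the traditional ED care track".

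For ASQ low-risk children at Alberta Children's Hospital, Protocol 2.1 describes a meeting with a nurse or social worker, after which families "will leave the ED within 30 minutes of arrival". At the Stollery, such children can use the clinic inside the hospital during its hours.

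Protocol 3.9 (Administrative) casts a wider net than 3.8: "data will be collected for any ED visits within 30 days of the participants' index ED visit". The fields include presenting complaint, triage acuity, whether the child was admitted, and discharge diagnosis. Objective 4 in Protocol 1.2 also names ED revisits, without limiting the cause.

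**The concern.** A balancing measure should be able to show the harm that the change itself could cause. Here a central change to ED care is that a physician's medical check is no longer routine for high-risk children. The harm specific to that change is a medical condition that goes unrecognised, for example an organic cause behind a presentation triaged as bizarre behaviour, which is an eligible complaint under Protocol 3.4. Such a child would come back, or be admitted, under a medical diagnosis, and that falls outside all three listed event types.

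The study could therefore report that its balancing measures showed no unintended consequence while medical returns had risen. The data to see the rise would be in the study database, but nothing in the protocol says anyone will look at them for that purpose.

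**Working it through.** The protocol states no figure on this point, so there is none to reproduce. The check sets the sections side by side.

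| Protocol section | Causes of ED return covered | Role given to it |
|---|---|---|
| 1.2, objective 4 | not restricted | healthcare delivery objective |
| 3.8, process outcomes | ED revisits not listed | none |
| 3.8, balancing measures | mental/substance use; self-harm (plus completed suicide) | identify unintended consequences |
| 3.9, Administrative | any ED visit within 30 days | data collection only |
| 3.11 | ED revisits not mentioned | none |

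1. **Are medical events among the balancing measures?** Of three listed event types, none is medical.

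2. **Would a medical return be recorded?** Yes, under 3.9, if the participant gave written consent to record review and returned to an ED within 30 days.

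3. **Does another outcome in 3.8 use it?** The admissions outcome covers visits for mental healthcare. The monthly record audit compares assessments with discharge recommendations. Neither is defined to find a missed medical condition.

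4. **Does another part of the plan examine it?** The example improvement cycle in 2.4 tests the removal of medical clearance, but the measures it names are length of stay and feedback from staff and families.

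5. **What would escape even the 3.9 data?** Conditions found in the urgent care clinic or elsewhere outside an ED, returns after 30 days, and events in patients without written consent. Deaths other than suicide are also outside the balancing list.

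6. **Which data stream feeds which measure?** The balancing measures are run by the Institute of Health Economics on Alberta Health data. Section 3.9 lists six items that the study passes to that institute (identifier, enrolment date, cohort, age and gender, partial postal code, wellbeing scores). The 30-day visit fields are not among them, so they sit with the main study team.

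**Illustrative size.** Protocol 3.10 gives at least 50 followed patients per interval and at least 8 intervals. Protocol 2.4 gives a 12-month maintenance phase. The rate of medical problems that clearance would have caught is not in the protocol; 0.5% to 2% is assumed.

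- 12 months: 50 × 12 = 600 per site; 0.005 × 600 = 3 and 0.02 × 600 = 12 events.
- 8 intervals: 50 × 8 = 400 per site; 0.005 × 400 = 2 and 0.02 × 400 = 8 events.

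These overstate missed cases to the extent that the physician routes in 2.2 and 3.5 catch some. The 50 also reflects 1-month survey follow-up, so it is only a rough denominator for a record-based measure.

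**The case against.** A reader might infer that a missed medical condition could never come to light in this study. The protocol does not support that. Section 3.9 collects ED returns of any cause with a discharge diagnosis, and objective 4 in 1.2 names ED revisits without restriction. The gap lies in what is counted and examined as a harm, not in what is recorded.

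A reader might also infer that high-risk children have no access to a physician. That is wrong too. Evaluation follows if a concern emerges or the family asks (2.2), families can stay to be seen by an ED physician (3.4), and a switch to traditional care is open at any point (3.5). Improvement cycles are meant to catch unintended effects (2.4). These routes lower the risk but do not measure it, and a condition that nobody suspects need not trigger any of them.

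Three further objections have force:

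- An undisclosed ingestion is a weak example. If it was intentional, the return could be classed as self-harm and so be counted. Known significant self-harm and features of psychosis are already excluded from the bundle (3.5).
- The economics sub-project has its own protocol, and a statistical analysis plan may exist; neither is shown. Either might define more. Still, the list of event types is fixed in this document, and the point is about that list rather than missing statistical detail.
- Medical returns will be few and mixed with unrelated paediatric visits, so a before-after contrast will be hard to interpret. This limits what the added measure can show, but is no reason to leave the events uncounted.

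**Conclusion.** The point holds in this form: the only measures designated to identify unintended consequences contain no medical event, although routine medical clearance is removed for ASQ high-risk children. A medical return within 30 days by a consenting participant would be recorded, but no outcome in 3.8 and no analysis in 3.11 counts it as a harm. The scope of ED revisits is also inconsistent: unrestricted in 1.2, restricted by cause in 3.8, any visit in 3.9.

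This rests on the text alone and needs no event rate. The 3 to 12 events per site (2 to 8 with eight intervals) depend wholly on the assumed 0.5% to 2% and show only the order of size. They are not evidence that harm will occur. The point takes no position on whether medical clearance should be part of care. It is a worthwhile and inexpensive improvement to harm detection and does not threaten the primary analysis.

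**What to change.** 1. Have the main study team add all-cause ED revisits and admissions within 30 days of the index visit as a balancing measure, using the data it already collects under 3.9. Placing it with the main team avoids mixing this stream with the institute's Alberta Health data.
2. Report it in three groups by discharge diagnosis: mental health/substance use, self-harm, and medical. Tabulate by phase and site, with the pre-implementation phase as the background rate for unrelated medical visits.
3. State that it is a descriptive safety signal among consenting participants, not a powered comparison.
4. Align 1.2, 3.8 and 3.9 on what counts as an ED revisit.
5. Add death from any cause if the linkage named in 3.9, which lists coroners' data as an example, can supply it.

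The cost is outcome wording, a rule for assigning discharge diagnoses to the three groups, and one more tabulation. No new revisit data are needed; all-cause death depends on the linkage. The downside is noise from unrelated visits, which the pre-implementation rate helps to calibrate.

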## **3.9 Data collection process**

We will use REDCap, a secure-web based application, to collect non-routine, outcome data from families (e.g., satisfaction, wellbeing). No additional data will be collected in the ED in order to minimize the impact on families during a time of crisis. Following the ED visit (24-72 hours later), using demographic data provided at registration, participants will be contacted at which time they will be asked to participate in this initiative. Eligible participants and/or their families may choose to decline and this will not affect their care. Participants who consent/assent can complete measures immediately. They will be offered the option of completing the data collection surveys by phone or electronically via REDCap (through their computer or mobile phone).

### ***Administrative***

Daily medical record review by research assistants will include collecting data on the number of bundle-eligible children/youth, number of children/youth with urgent clinic appointment booked based on ASQ screen at ED triage, and HEADS-ED assessment outcomes. Administrative databases will be accessed to collect: length of ED stay, time of admission to ED, time of discharge from ED, the Canadian Triage and Acuity Scale (CTAS) and the number of children/youth who received urgent care clinic appointment within 48 hours. Also, data will be collected for any ED visits within 30 days of the participants' index ED visit including the re-presentation visit triage date and time, the chief complaint, admission status, CTAS score, and discharge diagnosis. The Calgary team will access Edmonton's site participants' ConnectCare for the data collection within 30 days of the index ED and also the CTAS score from the index ED visit.

The PI will provide the full name, age, and Alberta personal health number (PHN) of study participants enrolled in the pre-implementation bundle and post-bundle implementation periods with Alberta Health to enable linkage to administrative healthcare databases in the economics analysis project (e.g., NACRS, ACCS, DAD, Alberta Health, Coroners' Data).

To enable the analysis in the economics sub-project, the PI will provide investigators at the Institute of Health Economics with study participants':

1. Study screening ID (generated for study administrative purposes)
2. Date of enrolment (to confirm study phase)
3. Assigned cohort (pre-implementation or post-implementation; to confirm study phase)
4. Age and gender

5. Forward sortation data (participant disclosed 3 first digits of postal code) at time of enrolment

6. Well-being scores

### ***Patient-reported***

Data will be collected electronically using REDCap or by phone. Participants will provide an email/phone number for email/text mailing of surveys or administration over the phone, as selected by participants.

The table below summarizes collection from youth and parents/caregivers.

| Baseline
(24-72 hours post ED visit) | 1-Month Follow-up        | 3-Month Follow-up | 6-Month Follow-up |
|-----------------------------------------|--------------------------|-------------------|-------------------|
| - SCWBS/WEMWBS
- SSS-10
- FQOL    | - SCWBS/WEMWBS
- FQOL | - SCWBS/WEMWBS    | -SCWBS/WEMWBS     |

### **3.10 Sample size**

Each series in our design includes at least 8 measurement time-points (intervals). In 2017, the Alberta Children's Hospital and Stollery Children's Hospital provided mental healthcare to 150–200 children/youth per month. Based on an anticipated consent rate of 75% and 1-month follow-up rate of 75% during each phase, we will have  $\geq 50$  patients/interval. We conducted preliminary calculations for the series with the fewest number of data points (8) and patients (50/month) using a 2-sample t-test comparing mean values in the pre-implementation phase to those in the maintenance phase. These calculations assume no serial autocorrelation and a sustained effect of the bundle, which is justified based on the PDSA cycles that will have occurred. With at least 800 patients in both the pre-implementation and maintenance phases, respectively, we will have 90% power to detect an absolute improvement as small as 1.9 units on the SCWBS/WEMWBS (primary outcome), assuming a common standard deviation of 10 using a 2-sided 5% level of significance. Thus, we are well powered to detect a difference of 3 units at each study site, the minimally clinically important difference defined for this outcome. We are below the effect observed in other studies using the WEMWBS. These preliminary calculations will be updated once baseline data become available.

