### *Pre-implementation phase*

Sites will begin with a 12-month period where there are no active, systematic, mental healthcare delivery innovations introduced. This phase will serve to provide the collection of baseline outcome measurements. During the last 2 months of this phase, a change management team at each site will follow Prosci®; a structured methodology with practical tools to support changes in healthcare practices. To help teams organize the phases of change during bundle implementation, we are using Normalization Process Theory. Each site will include a change management lead, change specialist, 6 project team members, and 4 site champions. ED and urgent care clinic managers, patient care managers, nurse educators, and senior leaders will also be involved. The change specialist will work with site champions on training plans and change management strategies, identifying how the care bundle will impact individuals. Strategies will be informed by identifying individual and organizational risks, barriers, and enablers, and supported by a change management communication plan. The change specialist will create change management process maps, champion roadmaps, coaching and training plans for frontline providers, and a resistance management plan. These tools will support implementation in the next 2 phases. The change specialist will also create an electronic database to track adoption issues and progress. Completed change management components will be integrated into the project plan before implementation and reviewed quarterly for responsiveness to individual/organizational needs.

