### ***Maintenance phase***

In the final 12 months, we will stop testing and changing the bundle with PDSA cycles. We expect to achieve maximal system uptake and efficiency by the end of the implementation phase. During maintenance, we will monitor bundle performance with ED dashboards. Change specialists and site champions will use performance measures and site-specific change management strategies to ensure fidelity to the care bundle is high. Champions will share findings in real time with healthcare providers to further promote adherence to the bundle.

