**Child/youth wellbeing:** Wellbeing will be measured with the Stirling Children’s Well-Being Scale (SCWBS) for children aged <13 years and the Warwick-Edinburgh Mental Wellbeing Scale (WEMWBS) for youth aged 13.0–17.99 years. Both scales are required because they are designed for different age groups. The scales assess wellbeing over the previous 2 weeks, are validated across many cultures, and are endorsed for measuring and monitoring wellbeing. We will administer the SCWBS/WEMWBS within 24–72 hours (baseline) of the child/youth’s index ED visit and again at 1 month (primary outcome time-point). The 3-month and 6-month time-points will support assessment of longer-term improvement. These scales measure the same construct in 2 different age groups, so data will be standardized and then combined across age groups to derive a single wellbeing measure.

The SCWBS is a short, robust measure that asks children 12 questions about their emotional and personal wellbeing. The scale has been used to assess change in wellbeing in several studies. The SCWBS covers 3 domains (optimism, cheerfulness and relaxation; satisfying interpersonal relationships; clear thinking and competence) to form a single dimensioned scale of wellbeing. A 5-point response scale is used and scores range from 12–60 with higher scores representing a greater level of wellbeing. The scale was developed and standardized across 18 schools with 1849 children. It has excellent internal consistency (Cronbach’s  $\alpha=0.85$ ) and good test-retest reliability ( $r=0.75$ ).

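### Section 3.10: 800 patients per phase give a detectable difference of 1.62 units, not 1.9; the error is conservative, but n, its basis and its scale need restating

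*Protocol*

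**What the plan says.** Protocol section 3.10 gives a complete set of inputs for the wellbeing outcome:

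- Test: "using a 2-sample t-test comparing mean values in the pre-implementation phase to those in the maintenance phase".
- Sample: "With at least 800 patients in both the pre-implementation and maintenance phases, respectively".
- Variability and error rate: "assuming a common standard deviation of 10 using a 2-sided 5% level of significance".
- Result: "we will have 90% power to detect an absolute improvement as small as 1.9 units on the SCWBS/WEMWBS (primary outcome".

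The calculation is said to be for "the series with the fewest number of data points (8) and patients (50/month"), after a sentence that sets 8 intervals as a minimum for every series. The 50 per interval is also a minimum, and it is stated after applying 75% consent and 75% one-month follow-up. The section concludes that 3 units, its minimally important difference, can be detected at each site. It calls the calculations preliminary and says they will be updated with baseline data.

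Section 2.4 sets the phase lengths. For pre-implementation: "Sites will begin with a 12-month period". Implementation lasts 5 months. For maintenance: "In the final 12 months, we will stop testing and changing the bundle". Section 3.11 analyses monthly means by site.

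On the outcome, section 3.8 says of the two age-specific scales that "data will be standardized and then combined across age groups to derive a single wellbeing measure".

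**The concern.** Sample size, SD, significance level, power and test are all printed, so the detectable difference is fixed by arithmetic, and the printed 1.9 is not what they give. The surrounding text does not let a reader recover the intended sample size. It offers 8 points, 50 per month and 800 per phase without saying whether 800 covers one site or both, or how it follows from the other two numbers.

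The scale is a second gap. The detectable difference and the 3-unit threshold are in scale units with a single SD of 10. The analysed outcome is a standardised combination of a scale running from 12 to 60 and one running from 14 to 70, and the standardised metric is not named.

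These figures say what the study was built to detect and what size of effect matters. If the recruitment target could be 400, 600, 800 or 1,200 per phase, neither progress nor a small observed effect can be judged cleanly against the plan.

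**Working it through.** **Inputs (section 3.10).** n = 800 per phase, SD = 10, two-sided 5% (z = 1.960), 90% power (z = 1.2816), two-sample comparison of means.

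**1. Attempt to reproduce 1.9.** Detectable difference = (1.960 + 1.2816) × 10 × √(2/n).

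At n = 800: 32.415 × √(2/800) = 32.415 × 0.05 = **1.62**. The exact t-test also gives 1.62. The printed 1.9 is not reproduced.

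**2. Sample size for 1.9.** n = 2 × (32.415/1.9)² = 582.1, so **583 per phase**. If 1.9 is rounded from anywhere between 1.85 and 1.95, n lies between 553 and 615. Rounding does not reach 800.

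**3. Power for 1.9 at 800 per phase.** The standard error is 10 × √(2/800) = 0.5. Then 1.9/0.5 − 1.960 = 1.84, and Φ(1.84) = **96.7%**.

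**4. Variants tried.** At 800 per phase, a one-sided test gives 1.46 and 80% power gives 1.40. Reading 800 as the total (400 per phase) gives 2.29. An SD of about 11.7 would give 1.9 at 800, but the section says 10. None of these recovers 1.9 from the printed inputs.

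**5. Sample sizes that the section could mean.** Same formula, SD 10:

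| Per phase | One way it could arise | Detectable difference (90% power) | Power for 1.9 | Power for 3 |
|---|---|---|---|---|
| 400 | 8 × 50, one site | 2.29 | 76.6% | 98.9% |
| 600 | 12 × 50, one site | 1.87 | 90.8% | 99.9% |
| 800 | as printed | 1.62 | 96.7% | >99.9% |
| 1,200 | 12 × 50, two sites | 1.32 | 99.6% | >99.9% |

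Power for 3 units at 400 per phase: standard error 10 × √(2/400) = 0.707; 3/0.707 − 1.960 = 2.28; Φ(2.28) = 98.9%.

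**6. Where 800 might come from.** Two routes reach it, and the protocol states neither:

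- Pooled: 8 × 50 × 2 sites = 800.
- Per site: section 1.1 gives about 200 visits a month at each hospital in 2017 (2,406/12 and 2,397/12), so the 150–200 a month in section 3.10 reads as per site. Taking the lower end and removing the roughly 20% ineligible (section 3.5), 150 × 0.8 × 0.75 × 0.75 = 67.5 a month, and × 12 = 810. This route does not use the quoted 50 per month.

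**7. Intervals.** The phases have 12, 5 and 12 monthly points. None has 8. The two phases that the t-test compares have 12 each, which meets a minimum of 8.

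**8. Scale.** At SD 10, 1.9 units is 0.19 SD and 3 units is 0.30 SD. If the standardised metric has SD 10 (a T-score, for example, which is an assumption), the unit figures carry over unchanged. If it is a z-score, they must be restated as 0.19 and 0.30.

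**The case against.** The best defence is that nothing of substance fails. On the printed inputs the plan understates its power, and its working conclusion, 3 units at each site, survives even at 400 per phase. That stands.

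The 1.9 might also be right for an unstated analysed number: 800 enrolled less 25% loss at one month is 600, which gives 1.87. The section does not say this, and its 50 per interval is already net of consent and follow-up. If 800 was built from that 50, this reading deducts the loss twice. It does not repair the text.

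The calculations are labelled preliminary. That lowers the stakes, but baseline data would update the SD. They would not reconcile 800 with 1.9 or say whether 800 is per site.

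Four stronger readings are tempting, and the protocol does not support them:

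- **That 8 intervals contradicts 12 months.** The section sets 8 as a minimum and 12 meets it. What remains is that the series described as shortest corresponds to no phase.
- **That 800 and 1.9 were taken from two different designs.** The fit of 1.9 to 600 is suggestive, but the protocol does not show how either number was obtained.
- **That a two-site total was carried over to a per-site claim.** Step 6 shows that 800 can be reached per site as well as pooled.
- **That 3 units has no meaning on the standardised outcome.** A metric with SD 10 would make it exactly 0.30 SD. Choosing the reference distribution may properly belong in a statistical analysis plan. The protocol's gap is that it states a target and a threshold in units without tying them to the combined measure.

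**Conclusion.** The point holds as an error in a stated figure. With 800 per phase, SD 10, two-sided 5% and 90% power, the two-sample t-test detects 1.62 units. The printed 1.9 corresponds to about 583 per phase, and power for 1.9 at 800 is 96.7%. The error is conservative.

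A reader might infer that the study is underpowered. The printed inputs do not show that. A shortfall for 1.9 appears only at 400 per phase, which is not the stated number, and 3 units remains detectable there with 98.9% power.

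Two ambiguities accompany the error: whether 800 is per site or pooled, and how the 8-point series relates to phases of 12, 5 and 12 months. The unnamed standardised metric is a gap to close and not a demonstrated mistake.

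All of this is on the plan's own t-test basis, with SD 10 and no serial autocorrelation. It says nothing about the power of the segmented regression in section 3.11.

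**What to change.** In section 3.10, use one set of inputs. State the number of monthly points per phase, and the analysed (not enrolled) number per phase, both per site and pooled. Then give the matching detectable difference:

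- If 800 per phase is kept: 1.62 units, with a statement of whether 800 is per site or pooled.
- If the floor of 50 per month over 12 months is used: 1.87 units for 600 per phase at one site, and 1.32 units for 1,200 per phase pooled. Say that these are minimum numbers, since 50 is itself a floor.

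Either replace the 8-point series with the phase lengths in section 2.4 or say which series it refers to.

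Name the standardised metric in section 3.8, or point to where it is defined. Express the detectable difference and the minimally important difference on it; at SD 10 the 3-unit threshold is 0.30 SD.

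The cost is a few corrected figures in section 3.10 and one sentence in section 3.8. Nothing in the design, recruitment or data collection changes, and the edit can be made with the update already promised for when baseline data arrive.
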